#### Measuring multiple levels

One of the complexities of implementation is that different agents are involved over time (Additional file 1). Initially, system leaders (*e.g*., juvenile justice, mental health, school) are involved in the decision of whether or not to adopt an EBP, and they often assess implementation feasibility. Over time, the key players in the process shift from system leaders to agency leaders and practitioners, and clients receiving services. A measure of implementation must incorporate data from these multiple levels if it is to accurately capture the complexity at various points in the process.

#### SIC scores

Two scores are calculated for each SIC stage. First, the amount of time that a site spends in a stage is calculated by date of entry through date of final activity completed (*i.e*., Duration Score). Because the implementation process is nonlinear, the Duration Score takes into account that activities might not be completed sequentially within a stage. Second, the percentage of activities completed within a stage is calculated (*i.e*., Proportion Score). A site might quickly complete a stage, but not complete all of the activities within that stage. Including both the Duration and Proportion Scores allows for an evaluation of which of these (and the interaction) is most important for successful implementation, and if these findings differ by stage. A third score identifies the final stage achieved (Stage Score).

#### Predictive ability of scores

Saldana and colleagues [21] found that SIC scores predicted variations in implementation behavior for sites attempting to adopt the MTFC model. Based on stage Proportion and Duration Scores, sites were accurately identified (*i.e*., face validity) through agglomerative hierarchical cluster analyses. Employing Cox proportional hazard models, cluster membership was used to predict successful MTFC start-up. Successful program start-up was predicted by site performance, as measured by the SIC in the first three stages (*i.e*., predictive validity). Sites that completed implementation activities thoroughly (high proportion) but relatively rapidly (duration) were most likely to initiate service; sites that took longer to complete each stage and completed fewer activities had a significantly lower hazard of having their first placement within the study period (HR = 0.190, p = 0.01) than rapid and thorough completers. Implementation condition did not significantly contribute to this model (p = 0.33), suggesting that prediction using the SIC was not attributable to implementation strategy.

#### Mapping cost by stage

Another analysis from the same trial [19] demonstrated that the SIC could serve as a map for costing implementation procedures. Procedures included calculations of fees, expenses, and person hours necessary to complete each Stage. Differences in cost structures (*i.e*., the when and how much for resource allocation) were identified between the implementation conditions despite implementation of the same intervention (*i.e*., MTFC). Differences in costs occurred primarily during the pre-implementation phase. Patterns of resource allocation were identified; although some stages were less expensive for one strategy than the other, the less expensive strategy might require more person hours or effort. Such information is critical for decision-makers when determining resource allocation and viability of the implementation strategy.

#### Proposed adaptations of the SIC

Similar to the core components proposed by Blasé and Fixsen [14] as being essential for successful implementation, each of the eight stages describes key milestones that are necessary (*e.g*., completion of training). We propose to adapt activities within each stage to target the specific tasks necessary to complete implementation. Some activities are expected to vary by EBP, while others are expected to be common/universal, such as fidelity monitoring. Our previous work showed that the decision to implement a new practice is largely based on the community need [22], and this perception is likely influenced by what service sector is accessing the population. This study will sample EBPs in three service sectors (school, substance abuse, juvenile justice) and combine this data across the original EBP in child welfare to build hypotheses about the differences in implementation processes between four sectors.

#### Potential impact to the field

As noted, there is a dearth of standardized measurement of implementation process, milestones, and costs. This gap impedes efforts to help inform real world implementation efforts for both researchers and EBP adopters. Measures such as the SIC that can increase the understanding of implementation processes that relate to the successful adoption of EBPs are needed. Such measures have the potential to contribute to the development of implementation interventions designed to improve success rates for sites at-risk for faltering or discontinuing implementation efforts. The goals of this project are to extend the SIC to additional EBPs in key child and family service systems, to measure meaningful implementation outcomes, and to examine the potential generation of universal items across EBP implementation strategies. We propose a mixed methods strategy to increase understanding of what the SIC scores represent to end users and to researchers. We also will evaluate a strategy for mapping implementation resources by stage that could inform the creation of user friendly fiscal plans for implementation efforts.

### Preliminary studies

#### MTFC-SIC for real-world MTFC sites

To evaluate the potential of the SIC to be utilized in a non-research context, the MTFC-SIC was examined with real-world, usual implementation MTFC sites. Because the measure was developed as part of a research trial and sites were recruited, we wanted to test the measure with non-study sites to ensure that the SIC could be used to adequately measure implementation performance and outcomes outside of the context of a controlled research design. In collaboration with the MTFC purveyor organization, records from the 75 most recently implemented MTFC sites were examined retrospectively. Using the MTFC-SIC, activity completion dates were recorded. We discovered that the SIC was not as useful for sites with existing programs that were adding additional MTFC teams to their organization; expansion sites did not complete the implementation process as thoroughly as those sites that were newly initiating their first program (due to previously completing the full process with their first program). Therefore, we limited the data to 35 newly adopting sites. Outcomes from the MTFC implementation research trial were replicated. Sites were successfully clustered into groups and these clusters were used in a Cox proportional hazard survival model. Sites that took longer to complete their pre-implementation stages had a greater risk of discontinuing than those who completed their stages more rapidly (hazard ratio [HR] = 26.50, p-value < 0.002). In addition to demonstrating the reliability of SIC scores in describing implementation performance and outcomes, this preliminary work illustrates the ability for a purveyor to complete the SIC based on retrospective records of usual implementation activities.

#### MTFC-SIC measurement properties

The measurement properties of the MTFC-SIC also were evaluated. Several challenges for evaluating its psychometric properties were considered (*e.g*., scores include both dichotomous and time variables, meaning of missing data). Given these challenges, the reliability and validity of the MTFC-SIC items [23,24] were evaluated using IRT-based Rasch models [25]. Proportion items and Duration items were evaluated using dichotomous and Poisson [23] models [24,26] and their multilevel extensions (HLM) [27]. Psychometric analysis suggested that the SIC was both a valid and reliable measure of the implementation process for MTFC. For a full description of the challenges and psychometric outcomes, see Additional file 2.

## Methods

Although the primary aims of the described study are to determine if the SIC can be applied across EBPs from different service sectors and accurately predict successful implementation outcomes, data provided from this project will allow investigation of EBP-specific implementation outcomes. Analyses will include examination of the impact that site demographic characteristics have on implementation behavior and cost outcomes. Moreover, because of the stage independence of the SIC, the varying impact of behavior in different stages will be evaluated.

### Participating evidence-based practices

The developers of three widely implemented EBPs from three public service sectors serving children and families agreed to participate in the current project: Multisystemic Therapy (MST) from the juvenile justice sector [28], Multidimensional Family Therapy (MDFT) from the substance abuse sector [29], and a computerized version of Coping Cat (CC) from the school setting [30,31]. All three are recognized in the National Registry of Evidence-Based Programs and Practices (http://www.nrepp.samhsa.gov) and, similar to MTFC, use an ecological approach to address clinical needs for children and families. MST and MDFT are intensive community-based interventions for serious externalizing behaviors, whereas CC is an office-based EBP for severe anxiety. Although there are many EBPs, the selection criteria for inclusion in this study were: (a) EBP for child and family mental health within key service sectors (schools, juvenile justice, substance use) similar to the original model (in foster care); (b) large real-world uptake within the respective service sectors in order to conduct study procedures; and (c) EBP developers who expressed interest in using the SIC and in advancing understanding of the universal implementation elements shown to increase the successful uptake of EBPs.

The recruited EBPs all have a large implementation footprint for the service sectors in which they are adopted. MST purveyors have implemented MST in 38 states and 13 nations; MDFT across 11 states and 6 countries; and CC across the U.S. and 3 countries. All three EBPs report a strong likelihood of continued growth.

### Specific aim 1: adaptation and extension through retrospective and prospective analysis

Figure 2 provides a diagram of the overall study procedures. The start-up for each EBP was rolled-out over the first year. An initial one-day site visit was conducted with each of the developer/purveyor organizations to learn about the standard implementation process for the EBP. The PI and developers operationalized implementation activities and defined completion criteria for these activities. From this initial adaptation work, EBP-specific and universal activities within each stage currently are being mapped onto the SIC Stages.

**Figure 2 F2:**
[figure not shown]
Diagram of study procedures.

### Retrospective data mapping

#### Mapping

Each of the participating EBPs agreed to provide data related to previous sites that have already implemented the EBP, and this data collection is underway. Research assistants from each of the EBPs were trained by the PI to code retrospective data related to a minimum of 15 formerly implemented sites. This number of sites was selected because it balances time and other resource demands, is sufficient for observing variability in implementation activities, and is sufficient for conducting preliminary Rasch-based measurement models.

#### Modification

Based on an initial examination of how well activities appear to define the stages, modifications will be made to each version of the SIC as needed. This might include moving activities from one stage to another, deleting activities, or redefining them. This iterative process has occurred for all three of the EBPs, with further modifications expected at the completion of data analyses. If substantive modifications are needed, an additional 15 sites will be coded retrospectively to verify that any modifications improve the measure’s ability to accurately measure implementation. Collaboratively with the developers, a final EBP-specific SIC will be determined for use in prospective data collection.

#### Prospective data collection

Research staff at the EBP organizations will be trained on data collection procedures for all newly adopting sites. A point person has been identified at each organization to monitor when new sites contact the purveyor to consider implementing the EBP (Stage 1) and to begin tracking activity data on the sites. The purveyors will be trained to note the completion of implementation activities by sites and the resources (both fees and person hours) needed to complete them. Data will include site demographics of all new sites [32]. To ensure reliability of data collected, within each purveyor organization, both the data collection assistant and the EBP site coordinator will independently record 10% of data.

### Analytic plan

#### Scoring

Recalling that the implementation process is known to be nonlinear, the scoring of the SIC does not rely solely on chronological completion of activities or stages. It also does not assume that all sites will complete all activities in a stage or within a given timeframe. As described previously, each site will be given stage Proportion and Duration scores, and a Final Stage score.

#### Measurement properties

Both retrospective and prospective data will be evaluated using IRT-based measurement models (*i.e*., dichotomous & Poisson Rasch models for activity completion and time-to-activity completion) and software (*i.e*., WINSTEPS, FACETS, HLM). Four sets of analyses will be conducted: (i) retrospective, (ii) prospective, (iii) combined retrospective and prospective, and (iv) universal/combined across EBPs. To thoroughly assess the reliability and validity characteristics of each EBP-SIC version, psychometric analyses will evaluate activity and site distributions, reliability, fit, variance components, and dimensionality (*i.e*., replication of methods described in Additional file 2).

A critical assumption is that item difficulty estimates are stable across uses of an instrument [33]. Thus, the activity estimates from retrospective data will be compared to those from prospective data, with stable estimates supporting the EBP-SIC versions. Invariance of activities ‘common’ across EBPs will be evaluated. Assuming invariance, common item equating [34] will allow simultaneous calibration across EBPs. Multilevel formulations will provide activity, stage and site estimates for each EBP. Likewise, an IRT-based item bifactor model [35] will provide loadings for each activity on its given stage and on a general implementation dimension.

#### Power

For IRT models, statistical power refers to the precision of parameter estimates and standard errors. Based on Linacre [36], the smallest number of activities and sites (*i.e*., retrospective data) are sufficient for estimates accurate within ±1 logit, with the prospective (and combined) data affording even greater precision. The combined data also are sufficient for accurate estimation of multilevel Rasch models [37].

#### Implementation performance: hypothesis testing

Replicating procedures from the original MTFC implementation trial, agglomerative hierarchical clustering methods will be employed to find similarities within sites from each of the EBPs with regard to both Proportion and Duration scores for each stage. Sites will be clustered using each of these variables independently, as well as together. Cox proportional hazard survival models will be conducted with days-to-event as a time to event outcome for each of the three sets of clusters. The events analyzed will include significant milestones such as program start-up and certification. Additional significant events will be determined in collaboration with EBP developers in order to ensure that the SIC is able to accurately predict milestones that are meaningful to the developers. It is hypothesized that each SIC version will produce outcomes similar to those found for MTFC such that both Proportion and Duration are significantly related to successful implementation outcomes [21]. The appropriate rate and necessary proportions might differ between EBPs and service sectors. Universal items will be evaluated to determine if they are more critical than unique items for successful implementation. For any analyses that combine retrospective with the prospective data, this characteristic will be included as a covariate to evaluate any differences.

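### As specified, Cox models on Proportion-only, Duration-only and joint clusters test marginal association, but cannot separate the two scores' independent contributions, relative importance or interaction when the scores are correlated

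*Protocol article*

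**What the plan says.** The Background section on SIC scores defines a Duration and a Proportion score for each stage and explains why both are kept: "Including both the Duration and Proportion Scores allows for an evaluation of which of these (and the interaction) is most important for successful implementation". The same sentence extends the question to possible differences between stages.

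The milestone analysis appears under Specific aim 1, in the section on hypothesis testing for implementation performance. It declares a replication of the MTFC procedures, using agglomerative hierarchical clustering of sites on the stage scores: "Sites will be clustered using each of these variables independently, as well as together". Then: "Cox proportional hazard survival models will be conducted with days-to-event as a time to event outcome for each of the three sets of clusters". Its hypothesis is that "both Proportion and Duration are significantly related to successful implementation outcomes". The one covariate named in that section is data source, retrospective or prospective, and only where the two are combined: "this characteristic will be included as a covariate to evaluate any differences".

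No model is described that holds Proportion and Duration as separate terms. There is no product term and no rule for comparing the three cluster sets. The regressions under Specific aim 3 relate SIC scores to cost. That section says cost variations will be considered against milestones, but it gives no milestone model.

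**The concern.** A Cox model on Proportion-only clusters is not adjusted for Duration, and a model on Duration-only clusters is not adjusted for Proportion. If quick sites are also thorough, each score picks up part of the other's effect. The joint clusters do not resolve this, because moving from one cluster to another can change both scores at once.

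The MTFC trial result in the section on predictive ability of scores shows the pattern: "sites that took longer to complete each stage and completed fewer activities had a significantly lower hazard of having their first placement" (HR 0.190, p = 0.01). Those sites were both slower and less thorough, so the contrast does not say which feature mattered.

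The Discussion expects developers to use SIC findings to change their implementation process and to advise sites whether to proceed. Advice to move faster differs from advice to complete more activities. Three cluster analyses that all come out significant would not tell developers which advice the data support.

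**Working it through.** **Plan's own figure.** The article gives no sample size, event count or power for the Cox models; its Power section covers the IRT models only. There is nothing to reproduce, so the check is of model structure, with a simulation to show scale.

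**Step 1: what each planned model estimates.** Let P and D be standardised Proportion and Duration for one stage.
- Proportion clusters: hazard depends on cluster(P); D is absent.
- Duration clusters: hazard depends on cluster(D); P is absent.
- Joint clusters: hazard depends on cluster(P, D), one label for both.
- Needed for the question in the SIC scores section: log hazard ratio = b1·P + b2·D, then + b3·P·D.

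None of the three planned models contains b1 adjusted for D, b2 adjusted for P, or b3.

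**Step 2: size of the carry-over.** Suppose b1 = 0, |b2| = 0.8 per SD and the correlation is r, with a linear relation between the scores. The expected value of D given P is r·P, so the marginal log hazard ratio for P is roughly r × b2 in absolute value (an approximation for a Cox model):
- |r| = 0.3: 0.3 × 0.8 = 0.24, hazard ratio about 1.27 per SD
- |r| = 0.5: 0.5 × 0.8 = 0.40, about 1.49
- |r| = 0.7: 0.7 × 0.8 = 0.56, about 1.75

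A score with no effect of its own would show these marginal hazard ratios.

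**Step 3: simulation.** From the document: a minimum of 15 retrospective sites per EBP and three EBPs, so 3 × 15 = 45; 90 is twice that. Assumed: one P and one D per site, |b2| = 0.8, the correlations, Ward clustering with two clusters per single score and three joint clusters, the censoring time, and two-sided alpha 0.05. There were up to 200 replicates per scenario, so the simulation standard error at a rate of 0.27 is √(0.27 × 0.73 / 200) ≈ 0.03.

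Only Duration acting; share of runs in which Proportion-only clusters are significant:

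| Sites | r = 0 | \|r\| = 0.3 | \|r\| = 0.5 | \|r\| = 0.7 |
|---|---|---|---|---|
| 45 | 3% | 14% | 27% | 51% |
| 90 | 6% | 26% | 44% | not completed |

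The Proportion term in the two-score model is significant in 4% to 8% of runs. The joint-cluster model is significant in 72% to 85% (45 sites) and 95% to 98% (90 sites), although Proportion has no effect.

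A second simulation (about 1,200 runs per setting, hazard ratio 0.45 per SD of Duration, correlation -0.4 and -0.6) gave 20% and 39% for Proportion-only clusters at 45 sites, against 6% in the two-score model.

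**Step 4: interaction.** With both scores acting, the joint-cluster test is significant in 66% to 92% of runs at 45 sites without an interaction and in 62% to 91% with one. At 90 sites the ranges are 87% to 100% and 81% to 97%. A significant joint-cluster result therefore does not signal an interaction. An explicit product term with an assumed coefficient of 0.5 is detected in 52% to 67% of runs at 45 sites and 86% to 94% at 90. It is flagged in 2% to 7% when there is none.

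**Step 5: stages.** Each stage has its own pair of scores. Entering three stages together needs 3 × 3 = 9 terms. A rough check (400 runs, within-stage correlation -0.5, only Duration acting, all assumed) gave a false-positive interaction test in 12% of runs at 45 sites, 18% at 30 and 43% at 15. With one stage at a time the rates were 6%, 6% and 10%.

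**Limits.** At most 13 of 200 replicates per scenario in Step 3 were dropped for fitting errors, and some fits gave convergence warnings.

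**The case against.** A reader might infer that the stated hypothesis cannot be tested at all. That is not so. The hypothesis is that each score is related to outcome, in a declared replication, and separate cluster models test exactly that. For the same reason the 14% to 51% are not error rates for that hypothesis: a Proportion score correlated with Duration really is marginally associated with the milestone. The percentages matter only if the result is read as Proportion's own contribution. For prediction and early detection, a marginal predictor is legitimate.

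A reader might also infer that the analytic plan promises the comparison and breaks the promise. The sentence about relative importance and interaction is in the Background and says what having both scores makes possible. It is not an analysis commitment.

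The article may not list every model term; it refers to earlier procedures, and the section on predictive ability shows that implementation condition was examined alongside cluster membership there. That leaves room for further covariates. It does not change the stated predictors, which are cluster sets, and adding such covariates would not separate the two scores.

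Nor do the documents support treating EBP-specific clusters as a fault in themselves, or replacing them with one pooled model as the primary test. The hypothesis concerns each SIC version, the article expects rates and proportions to differ between EBPs, and a single three-parameter model would ignore the stage-specific scores.

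The gap between the reason given for keeping two scores and the models stated for milestones still stands.

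**Conclusion.** The point holds in a limited form. The planned Cox models answer whether Proportion and Duration are each associated with milestones. As specified, they do not answer which score contributes independently, which matters more, or whether they interact, unless the scores happen to be nearly uncorrelated or the joint clusters happen to form a full high/low by high/low grid. The plan ensures neither.

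Under the assumptions above, an inert Proportion score would look important in about one run in seven (14%) to one in two (51%) at 45 sites, against 4% to 8% in a two-score model. More sites do not cure this: at |r| = 0.5 the rate rises from 27% at 45 sites to 44% at 90. The correlations, effect size and cluster counts are assumptions, and the document gives no values for them. The structural conclusion does not depend on them; the percentages do.

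**What to change.** Keep the three cluster models as the MTFC replication. For each milestone event, add a Cox model fitted one stage at a time:

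- use only scores from stages completed before the event;
- enter continuous Proportion and Duration (logged if needed) together, then add their product;
- stratify the baseline hazard by EBP when data are pooled across EBPs;
- adjust for retrospective versus prospective source, as already planned for combined data.

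Base statements about relative importance and interaction on these models, and say that the cluster models show marginal association. Treat the product term and any score-by-EBP terms as exploratory.

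The change needs wording in the analysis plan and no new data. It has three downsides: functional form must be checked, there will be several stage-wise tests to report, and power for interaction is only moderate (about 52% to 67% at 45 sites for the assumed coefficient of 0.5).

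### The protocol says its two scores allow a judgement on whether Proportion, Duration or their interaction matters most, but the cluster-based Cox models it fixes give no mutually adjusted effect and no interaction test

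*Protocol article*

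**What the plan says.** Under SIC scores (Background), the article explains why two scores are kept for each stage: "Including both the Duration and Proportion Scores allows for an evaluation of which of these (and the interaction) is most important for successful implementation". The same sentence raises the possibility that the answer varies from one stage to another.

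Under Implementation performance: hypothesis testing (Aim 1), the scores enter the analysis through agglomerative clustering: "Sites will be clustered using each of these variables independently, as well as together". Cox models are then fitted with "days-to-event as a time to event outcome for each of the three sets of clusters". The hypothesis is that "both Proportion and Duration are significantly related to successful implementation outcomes". The only covariate named there is whether a site's data are retrospective or prospective, when the two are combined.

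The procedure being replicated is described under Predictive ability of scores. There "cluster membership was used to predict successful MTFC start-up", and the reported result is that "sites that took longer to complete each stage and completed fewer activities had a significantly lower hazard" of a first placement than rapid and thorough sites (HR 0.190, p = 0.01).

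**The concern.** The question in the Background is one of attribution: which score, or which combination, carries the association with success. The article does not leave the model open. It names three sets of clusters with Cox models for each, and that form cannot return the quantity in question.

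- A model on Proportion clusters alone, or on Duration clusters alone, estimates a marginal association. If the scores are correlated, it absorbs part of the other score's effect.
- A model on joint clusters assigns each site one label. It has no separate coefficient for either score and no product term.

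The MTFC contrast illustrates this. It sets slow, less complete sites against rapid, thorough ones, so the HR of 0.190 cannot be divided between speed and completeness.

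Attribution matters because the article intends to use the scores one at a time. Aim 3 seeks the best rate and the best proportion of activity completion. The Discussion expects developers might change their implementation process because lingering in pre-implementation predicts failure. If completeness were the driver and Duration only its companion, purveyors could be pointed to the wrong lever, or the reverse.

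**Working it through.** The article gives no site number, event count or power for the Cox models (its Power section covers only the precision of the item response models), so there is no stated figure to reproduce. The check has two parts.

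**1. What each planned model can estimate**

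| Model | Related to outcome? | Effect adjusted for the other score? | Interaction? |
|---|---|---|---|
| Proportion clusters | yes, marginally | no | no |
| Duration clusters | yes, marginally | no | no |
| Joint clusters | yes, for the combination | no | no formal test |
| Both scores and their product (not planned) | yes | yes | yes |

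**2. How often a score with no effect of its own looks predictive**

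Suppose only one standardised score acts, with log-HR β per SD, and the scores have absolute correlation ρ. One SD of the inactive score then shifts the expected active score by ρ SD, so the inactive score shows a marginal log-HR of about ρβ. With β = ln 2 = 0.693 and ρ = 0.5, this is 0.5 × 0.693 = 0.347, or HR = exp(0.347) = 1.41 per SD. Two clusters cut near the median of a normal score lie about 1.6 SD apart, giving exp(0.347 × 1.6) = 1.74 before attenuation.

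Two simulations were run. All their settings are assumptions except the site numbers 15 (retrospective minimum per practice), 35 (usual-practice MTFC sample) and 53 (MTFC trial), which stand in the article. Both use Ward linkage cut at two clusters, exponential event times and a two-sided 5% test.

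- *Simulation A*: only thoroughness acts, HR 2 per SD; three noisy stage scores per site; about 35% censored; 1500 runs per cell.
- *Simulation B*: only Duration acts, log-HR −1.0 per SD; one pair of scores; 30% censored; 1000 runs per cell.

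Share of runs in which the single-score cluster model for the inactive score is significant:

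| Sites | ρ = 0 | ρ = 0.3 | ρ = 0.5 | ρ = 0.7 |
|---|---|---|---|---|
| B, 15 | 4% | 7% | 11% | 21% |
| A, 35 | – | 9% | 16% | 25% |
| B, 35 | 4% | 12% | 25% | 49% |
| B, 53 | 5% | 19% | 40% | 71% |
| A, 60 | – | 11% | 24% | 42% |
| B, 100 | 5% | 28% | 65% | 93% |

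In A the spurious HR is about 1.6 at ρ = 0.5, close to the hand calculation, and 1.9 at ρ = 0.7. At 15 sites it is of similar size (1.6 to 2.1) but seldom significant. In B at 15 sites, 17% to 22% of runs had at least one fit that did not converge; those fits were left out, so that row is rough.

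With both scores as terms in one Cox model, the inactive score is significant in 5.6% to 6.4% of runs in A and about 4% to 8% in B. The product term was not evaluated in these two simulations.

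The joint-cluster model does not separate the cases. In B at 53 sites and ρ = 0.5 it is significant in 85% of runs when only Duration acts, 82% when only Proportion acts, and 99% when both act (log-HR 0.7 each).

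**The case against.** **The statement is in the Background and says what the scoring makes possible.** The stated primary aims are application across practices and accurate prediction. This stands, and it limits the point: for prediction a marginal association is valid. But the statement is the article's stated reason for keeping two scores, and no described analysis delivers it.

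**The Aim 1 hypothesis can be tested.** A reader might infer that the plan cannot test whether both scores relate to success. The text does not support that. It claims a relation, not an independent one, and the single-score models test exactly that. A significant result for a score that acts only through its companion is a correct marginal finding; the error would be to read it as importance.

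**Joint clusters might include discordant groups.** A reader might also infer that joint clusters must move both scores together. They need not. The article foresees sites that finish a stage quickly but incompletely, and contrasts among such groups would be informative. Nothing in the plan ensures that they arise.

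**A condensed article leaves terms to the analysis plan.** This is fair for covariate lists and details. Here the article does state the form of the outcome models, and that form does not match the question.

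**The sizes are assumed.** This stands. The MTFC contrast suggests that slow sites are also less complete, but does not quantify it. The sign is not certain either: Duration runs to the last activity completed, so doing more could lengthen it. The two-sided rates above depend on the size of the correlation and not its sign, so a positive correlation would mislead equally often.

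**An adjusted model is weak within one practice.** This stands and shapes the fix. With only thoroughness acting (HR 2 per SD) and ρ = 0.5, a simulation of the three-term model had the interval for the difference exclude zero in 12%, 26% and 42% of runs at 15, 35 and 60 sites. A check with noise-free scores and 35% censoring gave 17%, 36% and 54%.

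**Conclusion.** The point holds as a mismatch between a stated use of the scores and the models described. The three cluster-based analyses support prediction and a marginal test of each score. They do not show which score matters more, whether the scores interact, or whether either answer differs by stage.

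Misattribution requires correlated scores: at zero correlation the single-score models keep an error rate near 5%. For assumed correlations of 0.3 to 0.7, an inactive score is significant in about 9% to 49% of runs at 35 sites, and in 7% to 21% at 15 sites in the stronger-effect simulation, against about 5% with both scores in one model. These figures rest on the assumed correlation, effect size, censoring and two-cluster solution. They show that the risk is material, not how large it will be in this study. The point does not undermine the prediction aim.

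**What to change.** Keep the three cluster analyses as the replication and prediction analysis. Add to Implementation performance: hypothesis testing:

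- One Cox model pooled across practices, stratified by practice, with the retrospective/prospective covariate, containing standardised Proportion, standardised Duration and their product.
- Scores taken only from stages completed before the event, with the summary across stages defined in advance (for example, one pre-implementation summary over Stages 1 to 3 for start-up). Stage-specific fits are exploratory and address the by-stage question. State where the event clock starts, since Duration is itself elapsed time.
- Duration reversed in sign so that both scores point towards success. Any statement on relative importance rests on the adjusted HRs per SD and the confidence interval of the difference between their logarithms; any statement on interaction rests on the product term. Neither is read from which single-score model is significant.
- Per-practice fits reported as descriptive.

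If this model is not wanted, withdraw the relative-importance and interaction statement under SIC scores and describe the results as prediction only.

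The cost is analysis wording and no new data. Intervals will be wider than for a single cluster term, the per-practice comparison will often be inconclusive, and pooling assumes that the two scores act similarly across practices, which the article itself says may not hold and which should be examined.
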